**Figure 1 F1:**
[figure not shown]
Flowchart of service users aged 18 years and above in the Multi-disciplinary Evaluation of Sexual Assault Referral Centres (SARCs) for better Health cohort study.

### Data collection

The form used by SARC staff to screen service users for the research provides data on gender; age; ethnicity; offence characteristics; referral into SARC and indicators of vulnerability at the point of service access (eg, history of mental health problems, disability, substance use). At baseline, we collect additional detailed sociodemographic information on marital/relationship status; nationality; immigration status; number of children; sexual identity; disability; religion; education; employment status and income; and accommodation. Baseline data is gathered using structured interviews, by telephone, video link or in-person by trained research staff who enter responses directly into secure bespoke study software linked to Qualtrics survey software. We enquire about adverse childhood experiences using the WHO ACE International Questionnaire and screen for lifetime and past-year domestic abuse using the ACTS^30^ to enable us to describe the sample. All other baseline measures focus on standardised timeframes according to the measure, or the period since participants attended the SARC. Follow-up is taking place on two occasions over the course of the project, at 6 months and 12 months. Our proposed methods for retaining participants are informed by a number of large studies of violence and health^31^ including our own previous work in the health field.^32^ These include gathering a range of contact details from participants at baseline - safe telephone numbers; postal/email addresses; use of reminders; and providing a small incentive (ie, £10 voucher following completion of baseline and 6 months and £15 voucher at 12 months).

### Outcomes

Table 1 shows the measures at each time point. The primary outcome is PTS, widely endorsed in the literature^5 10^ and through our scoping work with individuals with lived experience and service providers, as a primary health issue for survivors and an absence of diagnosis, or reduction in symptoms, may mark improvement or recovery in a person who has experienced sexual violence. Our analyses will focus on change or improvement in PTS symptoms between baseline and follow-up. We have developed a set of items to assess sexual health, including STI diagnosis; pregnancy and pregnancy outcomes, and reproductive coercion.^33 34^ Though we screen for sexual violence re-exposure at follow-up, discussion of the experience of sexual violence that led the person to seek help at the SARC is not encouraged in order to protect victims’ testimonies and to create a safe space for the person to participate in the research. Our approach to measuring health and other costs using the ICECAP-A^35^ and EQ5D-5L^36^ is outlined in the Economic evaluation section. We have also developed a comprehensive evaluation of SARC service users’ onwards service utilisation and satisfaction with care that considers the many sectors that are implicated in meeting the needs of survivors in the aftermath of an assault or abuse.

**Table 1 T1:** Outcome measures and the timepoint at which they are collected

Outcome	Measure	Timepoint
Post-traumatic stress	PCL-5^28^	Baseline, 6 months, 12 months
Depression	Centre for Epidemiologic Studies-Depression Scale (CESD-R-10)^51^	Baseline, 6 months, 12 months
Quality of life	WHOQoL-Bref^52^	Baseline, 6 months, 12 months
Eating issues	SCOFF^53^ BEDS-7^54^	Baseline, 6 months, 12 months
Health-related quality of life	EQ5D-5L^36^	Baseline, 6 months, 12 months
Capability	ICEpop CAPability measure for Adults (ICECAP-A)^35^	Baseline, 6 months, 12 months
Sexual health	Bespoke measure	Baseline, 6 months, 12 months
Alcohol use	AUDIT-C^55^	Baseline, 6 months, 12 months
Drug use	DUDIT^56^	Baseline, 6 months, 12 months
Resource use	Bespoke measure	Baseline, 6 months, 12 months
Adverse childhood experiences	WHO ACE International Questionnaire^57^	Baseline
Intimate partner violence	ACTS 4 item screen^30^ Composite Abuse Scale (CAS- Short Form)^58^	Baseline 6 months, 12 months
Re-exposure to sexual violence	Bespoke measure	6 months, 12 months
Suicidality and self-harm	Items from the Adult Psychiatric Morbidity Survey^59^	Baseline, 6 months, 12 months

PTS, post-traumatic stress.

### Patient and public involvement

The funding application for this research was made in response to a commissioned call from the National Institute for Health Research (NIHR) which set out a series of research questions concerning the evaluation of SARCs in England. We met with survivors of sexual violence as well as other stakeholders (eg, rape crisis services, SARC staff) and consulted them throughout the funding application process to ensure that the proposed research met the diverse needs of survivors and providers, and was acceptable and feasible from their perspectives. When funding was awarded, we formalised Patient and Public Involvement (PPI) by recruiting a group of survivors to support the study on an ongoing basis. Members named the PPI group as the Lived Experiences Group (LEG) and it is made up of 10 survivors from different backgrounds and experiences. Two members of the LEG sit on our study steering committee (SSC) and the wider group has been involved in every aspect of our study decision-making, the design of our materials, our communications about the study and production of outputs, development of follow-on projects. The LEG will continue to support the process of understanding and interpreting our findings, shaping the recommendations we make, and disseminating effectively with all stakeholders, including our participants, about what we find.

### Data analysis

Our analysis will determine if variation in SARC service delivery and other healthcare specific to sexual violence is associated with different levels of improvement in trauma symptoms between baseline and the 12-month follow-up. Our favoured statistical approach will be to model ‘trajectories’ of PTS using mixed-effects regression (ie, multilevel modelling, using Stata’s suite of mixed-effects tools^37^). This framework will enable us to model variation in the improvement in PTS and make best use of the three waves of data available. In the eventuality that change appears non-linear, we will first explore the utility of incorporating varying times of follow-up and modelling time-since-baseline rather than data-collection-wave as the time axis, although we will be mindful of the potential for introducing bias by incorporating such a source of variation. We will also consider standard single-level regression models (eg, Ordinary Least Squares (OLS) regression, Analysis of Covariance (ANCOVA)) and model observed change in PTS between baseline and 12 months, instead using the 6-month wave to assist with the treatment of any missing data using multiple imputation. In addition, and where appropriate, we will accommodate the nested data structure of participants within SARC-centres using cluster-robust SEs. Similar analyses will be carried out for the secondary outcomes.

(1) Following the investigation of the optimal ‘unconditional’ model to describe changes in PTS and the other outcomes of interest, we will introduce SARC-level characteristics (whether ISVAs are located at SARC or externally provided; whether the SARC is run by police, NHS, voluntary agency or private company; regional capacity for meeting survivors’ needs; ease of access to SARC) and characteristics related to follow-on care for sexual violence and mental health (uptake of ISVA care, access to therapy in the NHS or elsewhere), as a series of fixed effects. (2) The next stage of analysis will seek to address the question ‘How do trajectories compare for different subgroups of survivors attending SARCs?’. In the event that the mixed models described earlier can be empirically justified, we will estimate outcome trajectories for different groups incorporating recent versus non-recent victimisation including time lag between trauma and SARC visit, ACEs, gender, sexuality, culture, ethnicity, disability and chronic mental health problems and perceived benefit/harm from services. Where necessary, the single-level equivalent for this analysis stage will examine whether mean differences in PTS improvement vary across the same participant characteristics. While this stage mentions ‘subgroups’, and technically involves an interaction (with time since baseline), this can be considered both conceptually, and in terms of statistical power, to be a series of main-effects analyses. (3) Finally, we will investigate the role that participant characteristics may have in moderating the benefits of different SARC factors and follow-on care for sexual violence and mental health. This analysis will be both exploratory and pragmatic given the likely low power for this step and will be driven by the findings from stages (1) and (2) above. We will focus on those minority groups large enough to enable robust statistical comparison and formal interactions tests to be performed. In instances where some subgroups of interest are small (eg, male survivors), hindering formal statistical tests, we will take a more descriptive approach and be cautious about our conclusions.

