### Sampling, recruitment and procedures

We have recruited a stratified random sample of 15 of all the current practicing adult SARCs in England (approximtely 50 identified at the time of writing) with strata defined according to service delivery model, size and level of integration of services. To do this, we have drawn on national indicators of performance data collected by National Health Service (NHS) England and NHS Improvement,^15^ the commissioning body for SARCs, and data collected from SARCs as part of the wider MESARCH study.

Recruitment is taking place in three phases. First, service users aged 18 years and above presenting in person (or remotely since COVID-19) at any of the 15 participating SARCs are screened by SARC staff. People are excluded if, in exercising own judgement, the responsible member of SARC staff conducting screening anticipates a service user may encounter difficulties in providing informed consent due to severe mental health issues, cognitive impairment or learning disability. We also exclude those visiting from prison settings, as conducting follow-up assessments in prisons is outside the scope of the project. SARC staff complete a screen form for all those over 18 presenting to the service, recording basic demographic data, and offence and referral characteristics and indicating whether the person is eligible or not, with any reasons for exclusion noted. These screen forms are given an identification number, contain no identifying information, and are passed to the project team to provide an indication of the characteristics of the pool of service users pre-enrolment.

Because many SARCs refer on quickly to other voluntary sector agencies (ie, non-governmental organisations (NGOs)), for each participating SARC, we identified all linked support agencies and worked to engage them. The second phase of recruitment mainly takes place in that follow-on setting. When the person is referred to follow-on services, the identification number assigned at SARC travels with them. The study is introduced in that setting by trained staff from the agency, and if the person/service user expresses an interest in hearing more about the study, the staff member seeks consent to pass on contact details to the researchers. The identification number is also passed to the research team at this point, thus allowing the researchers to link the person/contact details with the SARC data obtained in the first phase.

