
### Number of participants required

At each of the 15 participating SARCs and via some self-referral, eligibility and basic sociodemographic data are collected on a total of 2500 individuals enabling us to compare our cohort sample with the wider population of service users at SARC. The primary outcome of interest for evaluating service user journeys after attending a SARC is PTS, measured using the PCL-5.^28^ Our interpretation of models based on the PCL-5 will focus on what constitutes a minimal clinically important difference (MCID) for PTS. Stefanovics and colleagues^29^ concluded that differences of approximately 0.5 of an SD could be deemed clinically important both cross-sectionally and for within-person change. Since our study involves neither randomisation nor placebo-control, our analyses will focus on change in PTS symptoms between baseline and follow-up. We will take recommendations of Stefanovics *et al*^29^ as quantifying the change-score group-difference we would expect which separates a treatment that is effective from one that is ineffective. Based on guidelines,^28^ we anticipate this MCID of 0.5 SD to approximate to a 10-point difference on the PCL-5 change-score; however, Stefanovics *et al*^29^ propose that an SD-based approach would be more robust and we also recognise that the magnitude of change in on the raw-scale metric will be influenced by the length of time between baseline and follow-up.

To allow for four levels in a predictor variable (eg, four types of SARC service provider); up to 10 covariates; two time points; an expected small-to-moderate Cohen’s f, which corresponds to the MCID for our primary outcome variable^29^; and an α error probability of 0.05, 270 participants would be required at study end to achieve a power (1−β error probability) of 0.90. Based on previous studies,^19 20^ our pilot work, and recruitment and retention to date, we estimate attrition at 20% by 12-month follow-up, requiring a baseline target of 338 individuals (see estimated flow of participants in figure 1). Participants who do not complete a 6-month follow-up will still be eligible to complete 12-month follow-up measures.

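### For the four-level provider type, uncorrected cluster-robust standard errors on about 15 SARCs reject a true null far more often than 5%

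*Protocol article*

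**What the plan says.** - **Sampling** (Sampling, recruitment and procedures): "We have recruited a stratified random sample of 15 of all the current practicing adult SARCs in England". People who attended any other SARC in England during recruitment could also enrol by contacting the research team directly.
- **Sizing** (Number of participants required): the calculation allows for "four levels in a predictor variable (eg, four types of SARC service provider"), with "up to 10 covariates; two time points" and "an expected small-to-moderate Cohen’s f, which corresponds to the MCID for our primary outcome variable". It concludes that "270 participants would be required at study end to achieve a power" of 0.90 at an alpha of 0.05. No numerical f and no clustering term is given.
- **Predictors** (Data analysis, stage 1): the SARC-level characteristics are ISVA location, "whether the SARC is run by police, NHS, voluntary agency or private company", regional capacity and ease of access. Uptake of ISVA care and access to therapy enter at the same stage and vary between people.
- **Clustering** (Data analysis): the favoured approach is mixed-effects regression for trajectories over three waves, with OLS or ANCOVA of change as an alternative. On nesting within SARCs the section says: "where appropriate, we will accommodate the nested data structure of participants within SARC-centres using cluster-robust SEs".

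**The concern.** Provider type does not vary within a SARC, so evidence about it comes from differences between SARCs. Fifteen SARCs over four types average 15/4 = 3.75 per type. A sandwich variance is justified when clusters are many. Here, for each provider type, it rests on the spread of two to six SARC totals. The estimate is then biased downward and very noisy, yet it is referred to a distribution that treats it as well determined.

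This matters because the comparison of delivery models is part of the main analysis. The findings are to be taken to the commissioners of SARCs, and significant differences in effectiveness between models are the stated trigger for the longer-term economic model. A nominal 5% test that really runs at 20% or more could rank providers on noise.

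**Working it through.** **1. The plan's own figures.** f is not stated, so 270 can only be back-solved. For ANCOVA with 4 groups and 10 covariates, lambda = N × f² with 3 and 270 − 4 − 10 = 256 df. Power of 0.90 needs f = 0.231, since 270 × 0.2309² = 14.4. That is consistent with a small-to-moderate effect. The baseline target follows: 270/(1 − 0.20) = 337.5, rounded up to 338. Neither figure contains a clustering term.

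**2. Why the sandwich fails here, whatever the ICC.** Take equal SARC sizes and a provider type held by m SARCs. The sandwich estimate of the variance of that type's mean has expectation (m − 1)/m of the truth. The usual finite-sample multiplier is (15/14) × (269/266) = 1.083.
- m = 4: 0.75 × 1.083 = 0.81
- m = 3: 0.667 × 1.083 = 0.72
- m = 2: 0.50 × 1.083 = 0.54

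Each estimate rests on only m − 1 degrees of freedom, while the test assumes 14 or infinitely many. With equal sizes the statistic depends on SARC means only, so the over-rejection is the same at ICC 0 as at any other ICC.

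**3. Simulated null for the 3-df provider test, nominal 5%.** From the article: 15 SARCs and 270 people, so 18 per SARC if equal. Assumed: the split across provider types, the SARC sizes (equal, or ranging from 3 to 50) and ICC 0-0.05. Outcomes are change scores; runs used 2,000 to 4,000 replicates per cell.

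| Split and sizes | Cluster-robust, F(3,14) | Cluster-robust, chi-square | No adjustment, ICC 0.02 | No adjustment, ICC 0.05 | SARC means, F(3,11) |
|---|---|---|---|---|---|
| 4/4/4/3, equal | 20-22% | 28-30% | 12% | 23% | 4-6% |
| 6/5/2/2, equal | 35-38% | 43-45% | 12-13% | 23-24% | 4-6% |
| 4/4/4/3, sizes 3-50 | 31-36% | 40-45% | 16% | 31% | 4-5% |
| 6/5/2/2, sizes 3-50 | 49-61% | 58-68% | 17% | 36% | 3-4% |

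A different unequal-size pattern gave 25-44% with F, so the unequal-size rows show direction better than exact size.

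**4. More SARCs through self-referral.** With a balanced four-level factor, rejection is roughly 10-16% at 30 SARCs and 8-10% at 50.

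**5. Two-level SARC factors tested alone (15 SARCs).** An 8/7 split with equal sizes gives 5-9%, and with unequal sizes 8-13%. A 12/3 split gives 12-22%.

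**6. What correct inference does to power.** With 18 per SARC the design effect is 1 + 17 × ICC: 1.34 at ICC 0.02 and 1.85 at ICC 0.05. The effective N is 270/1.34 = 201 and 270/1.85 = 146. At f = 0.231, lambda is 14.4, 10.7 and 7.8 for ICC 0, 0.02 and 0.05, and the F(3,11) test has power 0.76, 0.63 and 0.48. These powers rest on the back-solved f.

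**The case against.** **A SARC-level random effect may be intended.** The favoured approach is multilevel, the unconditional model is still to be chosen, and the cluster-robust sentence comes straight after the single-level alternatives. The article does not exclude a SARC random effect, and an analysis plan not shown may specify one with suitable degrees of freedom. This stands in part. A reader might infer that the plan rules out any other device, and the text does not say that. But the multilevel structure is introduced for repeated waves, and the one method named for SARC nesting is the sandwich, made optional. That is a stated method with poor error rates, not merely missing detail.

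**Fifteen is the lowest plausible count.** Self-referral can add SARCs, up to a national total of about 50. This lowers the inflation, but even 50 does not bring the provider test to 5%.

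**The magnitudes are assumed.** ICC, split and sizes are not in the article, and stratification by delivery model may have balanced the split. That supports giving ranges. The most favourable 15-SARC case examined still gives about 20%. The simulations used change scores, not the three-wave mixed model.

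**One joint model.** A reader might infer that all SARC characteristics enter together, which would make matters worse. The article speaks of a series of fixed effects, which can equally mean separate entry, so the point does not rest on a joint model.

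**Significance is not the sole criterion.** Interpretation is to focus on the minimal clinically important difference. Intervals that are too narrow mislead that judgement too.

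**Conclusion.** The point holds for SARC-level predictors, most clearly for the four-level provider type used for sizing. At 15 SARCs of equal size, the uncorrected cluster-robust test rejects a true null in about 20-38% (F on 14 df) or 28-45% (chi-square) of studies, and in more with unequal sizes. Both branches of the optional wording fail. With the adjustment, the test over-rejects even at ICC 0; without it, the rate is about 12-17% at ICC 0.02 and 23-36% at ICC 0.05.

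A reader might go further and conclude that the whole main analysis is badly inflated. The documents do not support that. ISVA uptake and therapy access vary between people and are not covered here, and a balanced two-level SARC factor tested alone with equal sizes runs at about 5-9%. Nor is it enough to make the cluster-robust adjustment compulsory. At ICC 0.02 with equal sizes, the unadjusted test (12-13%) is closer to nominal than the cluster-robust one (20-38%).

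**What to change.** For every model with a SARC-level predictor, replace the optional cluster-robust wording with inference on SARC-level degrees of freedom:

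1. Include a SARC random effect (intercept, and time slope if estimable), fitted by REML with Kenward-Roger or Satterthwaite degrees of freedom.
2. If that does not converge, analyse SARC-mean change. For provider type use F(3, G − 4), where G is the number of SARCs actually contributing; G = 15 gives 11 denominator df.
3. Do not use large-sample cluster-robust Wald tests for these predictors.
4. State that SARC-level characteristics are entered one at a time, with any joint model as a sensitivity analysis.

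Only the SARC-mean route was simulated here. It held 3-6% for provider type; a 12/3 two-level factor with very unequal sizes ran at about 6-8%. A random slope from 15 SARCs may not be estimable, hence the fallback.

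The change is to analysis wording; no extra data are needed. The cost is wider intervals and power for provider type below 0.90 (0.48-0.76 under the assumptions in the working), which should be acknowledged alongside the sample-size statement.

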**Methods and analysis:**

This is a mixed-methods protocol for a 1-year cohort study aiming to examine the health and well-being in survivors of sexual violence after attending a SARC in England. Quantitative measures are being taken at baseline, 6 and 12 months. Post-traumatic stress (PTS) is the primary outcome (target N=270 at 12-month follow-up). Secondary measures include anxiety, depression, substance use and sexual health and well-being. Using mixed-effects regression, our main analysis will examine whether variation in SARC service delivery and subsequent mental healthcare is associated with improvement in trauma symptoms after 12 months. An economic analysis will compare costs and outcomes associated with different organisational aspects of SARC service delivery and levels of satisfaction with care. A nested qualitative study will employ narrative analysis of transcribed interviews with 30 cohort participants and 20 survivors who have not experienced SARC services.

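### Stage 2 treats a self-rating of services as a participant characteristic and lets it feed stage 3; if rated during or after follow-up, its trajectory difference is not a subgroup or moderator effect

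*Protocol article*

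**What the plan says.** Stage (2) of the Data analysis section asks "How do trajectories compare for different subgroups of survivors attending SARCs". Its groups run from recency of victimisation, adverse childhood experiences and gender to "sexuality, culture, ethnicity, disability and chronic mental health problems and perceived benefit/harm from services". If single-level models replace the mixed models, the analysis "will examine whether mean differences in PTS improvement vary across the same participant characteristics", so the service rating is explicitly counted as a participant characteristic. The section considers this stage, both conceptually and for power, "to be a series of main-effects analyses".

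Stage (3) examines the role that "participant characteristics may have in moderating the benefits of different SARC factors and follow-on care", and this work "will be driven by the findings from stages (1) and (2) above".

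Table 1 lists no measure of perceived benefit or harm. The nearest description is in the Outcomes section, a "comprehensive evaluation of SARC service users’ onwards service utilisation and satisfaction with care". The article does not say at which wave the rating is taken, or whether it concerns the SARC or later care. The Data analysis section is cautious about low power and small subgroups, but does not mention reverse causation.

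**The concern.** Apart from the service rating, the stage 2 groups describe the person or the assault, and can be defined before any change in PTS is observed. Perceived benefit or harm is a judgement about what services did for the person. The outcome is change in PTS from baseline to follow-up. Someone whose symptoms have fallen has a reason to say that services helped, and someone who has worsened has a reason to say the opposite. If the rating is collected at 6 or 12 months, grouping by it may partly sort people by the outcome itself.

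The difference would then be reported beside those for gender or ethnicity as if it were of the same kind. Because stage 2 findings steer stage 3, a strong signal from the rating could also bring it forward as a candidate moderator of the benefits of care, where the result would be hard to interpret. The study means its findings to inform commissioning, so the distinction matters.

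**Working it through.** **The plan's own figures.** The section on the number of participants gives 270 at 12 months and 20% attrition: 270 / 0.80 = 337.5, rounded up to 338, which agrees. The 270 rests on an effect size f that is not given as a number, so it can be reproduced only under assumed values. The present point depends on neither figure.

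**Inputs for the illustration.**
- From the protocol: a minimal clinically important difference of 0.5 SD, put at about 10 PCL-5 points. This implies a change-score SD of about 10 / 0.5 = 20 points.
- From the protocol: 270 at study end and alpha 0.05.
- Assumed, because the documents give none: the correlation r between rating and improvement, a bivariate normal distribution, a split at the median of the rating (135 v 135), and no effect of the rated care on PTS. All of r is then due to improved people rating services higher.

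**Formula.** Let C be standardised improvement and R the standardised rating. Then E[C | R] = rR, and the mean of R above its median is sqrt(2/pi) = 0.798. By symmetry the upper-half minus lower-half difference in C is

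2 × 0.798 × r = 1.596r SD.

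A simulation of 1,000,000 draws for each r agreed to within rounding.

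| Assumed r | Spurious difference (SD) | PCL-5 points at SD 20 | Chance of p < 0.05, 135 v 135 |
|---|---|---|---|
| 0.1 | 0.16 | 3.2 | 26% |
| 0.2 | 0.32 | 6.4 | 75% |
| 0.3 | 0.48 | 9.6 | 98% |
| 0.313 | 0.50 | 10.0 | 98% |
| 0.4 | 0.64 | 12.8 | >99% |

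The difference reaches the protocol's 0.5 SD when r = 0.5 / 1.596 = 0.313.

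**When this applies.** Set beside each other, two sections leave the timing open. Design and setting puts baseline at four weeks or later, followed by 6 and 12 months. Data collection says that baseline measures may cover the time since the SARC visit. So:
- A rating taken at 6 or 12 months can be influenced by the change being modelled, and the table is relevant.
- A rating fixed at baseline cannot be caused by later change. It can still reflect baseline symptoms or recovery that happened before baseline, so adjustment for baseline PCL-5 is still needed.

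**The case against.** The strongest reply is that the documents do not say when the rating is made. A baseline rating of SARC care is compatible with the Data collection section, and an article commonly leaves the wave of one covariate to a fuller document. Stage 2 is also framed as a descriptive comparison, the study acknowledges that it is not randomised, and asking whether people who felt harmed by services follow a different course is legitimate. Stage 3 is labelled exploratory, is to focus on minority groups large enough to compare, and does not name perceived benefit as a moderator.

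Much of this stands, and it rules out several stronger readings that a reader might infer:
- That the rating is a consequence of recovery, or that the comparison is circular. The timing is not stated, and a service rating is a different construct from the PCL-5. The association may be reversed or confounded, but it is not circular by construction.
- That a large, significant difference is to be expected. Both r and the median split are assumed, and at r = 0.1 the difference is only 0.16 SD with a 26% chance of significance.
- That the economic evaluation repeats the fault. Comparison by "levels of satisfaction with care" appears only in the abstract; the economic sections compare organisational aspects and delivery models. That is a mismatch between abstract and body and lends no support here.
- That the variable must be deleted. A rating that precedes the change, or a separate descriptive report, is enough.

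The reply does not remove the classification itself. The article positively places a post-service rating among participant characteristics and lets stage 2 results drive a stage about moderating benefits, without restricting which rating may be used.

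**Conclusion.** The point holds conditionally. Stage 2 classes a self-rating that can arise only after service contact with pre-existing traits, and nothing stated keeps it out of stage 3. If the rating is taken during or after follow-up, a difference in PTS trajectory between those who felt helped and those who felt harmed cannot be read as a subgroup or moderator effect. If it is fixed at baseline, reverse causation by the modelled change is excluded, although confounding by baseline symptoms and earlier recovery remains.

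The possible size is about 1.6r SD under the stated assumptions, from 0.16 SD at r = 0.1 to the full 0.5 SD at r of about 0.31. These are illustrations of what a modest reverse association could produce, not estimates for this cohort. Neither the sample size nor the other stage 2 comparisons are affected.

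**What to change.** - In stage 2, use only a rating that precedes the change being modelled, namely the baseline rating of care already received, and adjust for baseline PCL-5. State the wave and which services are being rated.
- Report any rating from 6 or 12 months separately, as a descriptive correlate of change, with a sentence saying that the direction of the association cannot be determined.
- Exclude perceived benefit/harm from the stage 3 candidate moderators.

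The cost is one fewer formal subgroup if no baseline rating exists, and the loss of later ratings from the formal comparison. All data remain available for description. The change is one of wording, and the targets of 270 at 12 months and 338 at baseline stay as they are.
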